### 2.9. Statistics

Differences between the three groups will be analyzed. Normally distributed data will be analyzed using ANOVA and on abnormally distributed data, the Kruskal-Wallis test will be applied [37]. The ANOVA test will show if there is a significant difference between the groups and a post-hoc analysis will detect where the difference lies. In all analysis, intention to treat will be used.

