### 2.3. Instrumentation

An Inertial Measurement Unit (IMU) measures linear accelerations and rotational velocities, often combined with a GPS to reduce the drift in the position level [28,29]. Two different IMU’s will be used in the study: one for measuring postural sway and one for measuring body positions and movements. An IMU containing algorithms for measuring postural sway will be used in all three intervention arms and obtain measures of postural sway in the anterior-posterior and medio-lateral direction at baseline and at follow ups. The IMU used has shown good validity and reliability for measuring postural sway [13]. When measuring postural sway, the IMU is attached to the lower back and postural sway is measured when the participant is standing still, for 30 s. Another IMU, containing algorithms for measuring body positions and movements will be used in one of the intervention arms (intervention B). Body positions are time spent sitting, time spent standing or walking, time spent in supine, prone, and side lying. Movements measured are strides, step time, falls, near falls, and variation in gait. The algorithms in this IMU were developed within the Modern Technology against Falls (MoTFall) project and have shown good sensitivity and specificity for measuring a near fall [15]. When used in the intervention, the participant wears the IMU on the right thigh, approximately 10 cm above the knee, under the clothes, attached with skin-friendly adhesives. The IMU is worn 24 h per day and is charged twice a week. Data from the IMU is sent through a router mounted in the participant’s home, to a platform, where the PT can obtain the data simultaneously and follow the participant’s progress in the rehabilitation process. Data collected during time when the participant is too far away from the router is saved in the IMU and uploaded to the platform when the IMU is charged.

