### 2.5. Outcomes

The primary outcome is balance in terms of postural sway and functional balance. Measures of postural sway are performed with the patient standing with heels approximately 10 cm apart and feet pointing about 30° outwards for 30 s with eyes open (EO) and then 30 s with eyes closed (EC). During the measure, an IMU is mounted on the patient’s lower back, in level with L5. The IMU has shown good validity and reliability for measuring postural sway compared to the golden standard (force plate) [13]. Functional balance is assessed with the Functional Balance test for Geriatric patients (FBG), and grades the performance with points, where 0 stands for no execution and 6 for the higher level of performance. FBG evaluates the ability of the patient to sit and stand up, maintain a standing position, walk, and turn. The test includes four activities that the patient shall complete, and every activity has 7 levels of difficulty, indicating the level of independence in each task. The maximum points achievable is 24 [32]. The FBG has shown good validity and reliability when compared to the golden standard (Berg Balance Scale) [22].

Secondary outcome measures are functional independence in everyday activities, health-related quality of life, and the physiotherapist’s satisfaction with the IMU.

Functional independence in everyday activities will be assessed using The Barthel Activity of Daily Living questionnaire. Participants are asked how they manage various everyday activities such as food intake, locomotion, toilet visits, dressing, bathing, transferring, and continence. Ten activities are included, rated on a three-graded scale 0–2 with 0 indicating the worst condition/state and 2 the best condition/state. The maximum score is 20 [33].

Health-related quality of life will be measured by the EuroQol 5-Dimension Questionnaire (EQ5D). EQ5D is a generic instrument to measure mobility, self-care, everyday activities, pain, and anxiety, with five response alternatives, ranging from no problem to unable/extreme [34]. The EQ5D also consists of a visual analog scale, where the participant is asked to rate their health on a vertical scale, where 100 is the best imaginable health state, and 0 is the worst imaginable health state. EQ5D is widely used for monitoring health status among different patient groups all over the world [35].

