### 2.6. Procedure

Background data on age, sex, method of surgery for the hip fracture, and medication will be collected at baseline. All other measures will be collected at baseline and end of the rehabilitation period. Postural sway and balance will also be assessed 3 months after the end of the rehabilitation period. At the end of the rehabilitation period, physiotherapists fill in USEQ and also record how many home visits were performed and time spent at each home visit as well as the number of phone-calls each participant required.

Baseline data, including information about age, sex, method of surgery for the hip fracture, and medication, as well as outcome measures, will be obtained by a PT at a regular home visit. Follow-up measures will be performed at the end of the rehabilitation period, including primary and secondary outcome measures. The rehabilitation period is defined by the needs of the individual participant and can hence differ in time between participants.

At the end of the intervention treatment, the PTs will fill in the USEQ questionnaire regarding how satisfied they were with using the information from the IMU. During the study, PTs will document the duration and number of home visits as well as telephone calls. PTs time and number of visits is not a pre-designed factor, and it will adapt to the patient’s necessities. The treating PT will also take notes regarding participants who discontinue or deviate from the intervention’s protocols, including reasons for discontinuing or deviating.

All PTs in community healthcare in Malmö, who rehabilitate persons with hip fracture in the Malmö municipality, have received education in the HIFE program. Additionally, workshops including an introduction of the IMU, how to use it, and how to retrieve data from it have been performed. Inclusion of participants to the pilot and feasibility study started in May 2021 and is expected to be completed in December 2021. After that, any necessary changes to the study protocol will be made and a decision whether the full RCT should be conducted will be made.

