### 2.7. Sample Size

Since balance, measured by postural sway, is the main outcome measure, postural sway was used to determine the statistical power of the study. We used results from a previous study [25] with a mean value of 1.8 mm/s for difference in postural sway in the anterior-posterior (AP) direction between two groups of community-dwelling older persons. Since we want to calculate differences between all three groups, a significance level of 0.017 was determined, giving a necessary sample size of 43 participants in each group to reach a power of 80% [37]. To compensate for dropouts, the sample size was set to 48 participants in each group.

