### 2.8. Randomization

To enhance the power of the study, to reduce bias of covariates and ensure equal dispersion of the participants at all times [38], block randomization will be applied through a website [39]. The number of subjects in each block will be 48 and the number of blocks will be 3, generating a randomization plan with subjects randomized in 3 different treatment blocks.

An independent person will perform the randomization process. All baseline measures will be performed before randomization to any of the interventions. Blinding of the assessor is not possible at present, due to the restrictions caused by the Covid-19-pandemic, prohibiting unnecessary home visits. However, when these are lifted, follow-up measures at 3 months will be performed by an independent PT, not aware of which intervention the participants have been allocated to. Blinding of participants is not considered possible.

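### The balance outcomes are to be compared by ANOVA or Kruskal-Wallis with no baseline covariate, although sway and FBG are measured before randomisation; ANCOVA would be more efficient at no cost

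*Protocol article*

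**What the plan says.** Section 2.5 (Outcomes) defines the primary endpoint: "The primary outcome is balance in terms of postural sway and functional balance". Section 2.9 (Statistics) gives the method for comparing the three groups: "Normally distributed data will be analyzed using ANOVA and on abnormally distributed data, the Kruskal-Wallis test will be applied". After a significant ANOVA, "a post-hoc analysis will detect where the difference lies". All analyses follow intention to treat. Section 2.9 mentions no covariate, ANCOVA, mixed model or change score, and no other section adds one.

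The baseline values exist in every arm. Under section 2.3 (Instrumentation), the sway device is used in all three arms to "obtain measures of postural sway in the anterior-posterior and medio-lateral direction at baseline and at follow ups". Section 2.6 (Procedure) lists the background data taken at baseline only and then says: "All other measures will be collected at baseline and end of the rehabilitation period". It adds a later visit for the primary endpoint: "Postural sway and balance will also be assessed 3 months after the end of the rehabilitation period". Section 2.8 (Randomization) settles the order: "All baseline measures will be performed before randomization to any of the interventions".

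Section 2.7 (Sample Size) takes from an earlier study "a mean value of 1.8 mm/s for difference in postural sway in the anterior-posterior (AP) direction", uses a significance level of 0.017 for the three pairwise comparisons, and arrives at 43 per group for 80% power, raised to 48 for dropouts.

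**The concern.** A baseline measurement of the outcome, taken before randomisation, is usually the most useful covariate a trial has. It is available here for both primary measures, and the tests named in section 2.9 do not take it as a covariate. If follow-up values are compared directly, the part of their variance that baseline could explain stays in the error term. If changes are compared, baseline is used, but with a fixed weight of one, which adds noise when the correlation is modest.

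Section 2.8 says that one purpose of the randomisation scheme is to improve power and reduce covariate bias. Blocking equalises the numbers per arm. No stratification on baseline sway or FBG is described, so blocking does not serve that purpose for these variables. Adjustment would.

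A secondary matter is that the choice of test depends on the observed distribution. The rank route does not itself yield a difference in mm/s, the scale on which the trial was sized, and section 2.9 describes a pairwise step only after ANOVA.

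What is at stake is precision in a trial of 144 participants, with room for about 10% dropout (1 − 43/48 = 10.4%).

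**Working it through.** **Inputs from the protocol article.** Difference 1.8 mm/s in anterior-posterior sway, alpha 0.017, power 80%, 43 per group (section 2.7).

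**Assumptions.** The test is two-sided (sidedness is not stated). The standard deviation (SD) is that of a single sway measurement, equal at baseline and follow-up. The baseline to follow-up correlation r is not in the documents, so a range is shown.

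**Step 1: the plan's own figure.** No SD is given, so 43 cannot be reproduced from the stated inputs. It can only be inverted. The normal approximation gives

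d = (z₀.₉₉₁₅ + z₀.₈₀) × √(2/43) = (2.387 + 0.842) × 0.2157 = 0.696, so SD = 1.8/0.696 = 2.585 mm/s.

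With the t distribution (84 degrees of freedom), d = 0.708 and SD = 1.8/0.708 = 2.54 mm/s. The t-based value is used below; the normal approximation gives the same powers to the whole percentage point.

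**Step 2: variance relative to an unadjusted follow-up comparison.**

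- Follow-up value alone: 1
- ANCOVA on baseline: 1 − r²
- Change from baseline: 2(1 − r)

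**Step 3: power.** Divide d by the square root of the variance factor and evaluate the two-sample test at 43 per group and alpha 0.017. For example, at r = 0.5 ANCOVA has factor 0.75 and d = 0.708/√0.75 = 0.818, giving 91%.

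| Assumed r | ANCOVA factor | ANCOVA power | Follow-up only | Change-score factor | Change-score power |
|---|---|---|---|---|---|
| 0.2 | 0.96 | 82% | 80% | 1.60 | 57% |
| 0.3 | 0.91 | 84% | 80% | 1.40 | 63% |
| 0.5 | 0.75 | 91% | 80% | 1.00 | 80% |
| 0.6 | 0.64 | 95% | 80% | 0.80 | 89% |
| 0.7 | 0.51 | 98% | 80% | 0.60 | 96% |

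**Step 4: the same gain in other units.** At r = 0.5, 43 per arm with adjustment carries the information of 43/0.75 = 57 per arm without it. The difference detectable with 80% power falls from 1.80 to 1.80 × √0.75 = 1.56 mm/s. At r = 0.7 it falls to 1.80 × √0.51 = 1.29 mm/s.

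**Step 5: which reading of section 2.9 matters.** The ratio of the ANCOVA factor to the change-score factor is (1 − r²)/[2(1 − r)] = (1 + r)/2, which is below 1 for every r below 1. ANCOVA therefore beats change scores throughout the range, and it beats the follow-up comparison whenever r differs from zero. On the change-score reading, power falls below the planned 80% when r is under 0.5.

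These powers are for anterior-posterior sway on the ANOVA route. The variance factors apply to FBG as well, but the protocol gives no effect size from which to compute its power.

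**The case against.** Several points on the other side are sound.

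- **Validity.** A reader might infer that the planned comparison is biased or underpowered. The documents do not support this. Under randomisation the unadjusted comparison is unbiased, and the sample size was set without any stated allowance for adjustment, so a follow-up comparison keeps the planned 80%.
- **Certainty that baseline goes unused.** A reader might infer that the baseline values are simply discarded. Section 2.9 does not say so. It leaves open whether follow-up or change is analysed, and a change score uses baseline. At r = 0.7 the change score has 96% power against 98% for ANCOVA, a gap of two points.
- **Size.** The correlation is not in the documents, and it could be modest. The Discussion says baseline is taken shortly after discharge and that pain could then strongly affect a strength test. Section 2.6 lets the rehabilitation period vary by participant. At r = 0.2 to 0.3 the gain over a follow-up comparison is only two to four points.
- **Chance imbalance.** It would be too strong to say that a baseline difference passes in full into the result. It carries over in proportion to r, and over repeated randomisations the standard error already allows for it.
- **Test choice.** The rule linking distribution to test is stated in advance and is conventional. Nothing prevents reporting differences in mm/s beside a rank test. This part is secondary.
- **Level of detail.** Covariates and transformations are often left to an analysis plan, which is not shown, and the protocol expects possible changes after the feasibility study.

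The last point does not remove the concern, because the article does not leave the method open: it names the tests, and neither takes a covariate. ANCOVA is also more powerful than both readings at every correlation shown.

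**Conclusion.** The point holds as a missed gain in efficiency, not as an error that invalidates the trial. Section 2.9 names tests without a baseline covariate for outcomes that are measured in every arm before randomisation. Relative to an unadjusted follow-up comparison, ANCOVA adds about 2 to 4 percentage points of power at correlations of 0.2 to 0.3, 11 points at 0.5 and 18 points at 0.7. Relative to change scores, it adds 25 points at 0.2, 11 at 0.5 and 2 at 0.7. These figures rest on a two-sided test, an effect size inverted from the plan's own 43 per group, equal SDs at both times, and assumed correlations. That ANCOVA is the more efficient choice does not depend on the particular correlation; the size of the gain does. The change is worth making because it uses data that will be collected anyway.

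**What to change.** In section 2.9, make the primary analysis of each balance outcome a linear model of the follow-up value on arm and the baseline value of the same measure. Report the three pairwise adjusted differences with confidence intervals at the planned 0.017 level, that is 98.3% intervals. Fix one approach to skewness in advance, for example log-transformed sway, so that the quantity estimated does not depend on the observed distribution. Keep the Kruskal-Wallis test as a sensitivity analysis.

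The cost is a change of analysis wording. It needs no new measurements, visits or participants, and 43 per group (48 with dropouts) can stand, with any gain in precision kept as a margin. The revision already foreseen after the feasibility study is a natural point for it.

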This study protocol does not include any specific measure of muscle strength. However, functional balance, here measured in the FBG test, demands muscle strength and so does functional independence in everyday activities, here measured with the Barthel questionnaire. Strength has a relation to dependence in everyday activities [48]. Baseline measurers will be performed shortly after discharge from the hospital and a measure of muscle strength can therefore be highly influenced by pain. Additionally, we want to limit the total number of tests, since performing them can be physically challenging.

In intervention B, in addition to HIFE, data of body positions and movements are collected using an IMU. Data is collected via the IMU 24 h per day and transferred through an application to the treating PT giving him/her an opportunity to follow the participants’ progression in the rehabilitation process on a day-to-day basis. This also enables the PT to provide constructive feedback to the participants during the monitoring period. Wearable devices with a built-in accelerometer have shown the ability to provide accurate data with individual characteristics [49]. Laboratory, as well as home-based studies, have shown that accelerometer technology can accurately evaluate balance and risks of falls in an older population [50]. However, whether this has any effect on the outcomes of rehabilitation has, to our knowledge, not been studied before. In addition, concerns regarding patient privacy, management of system operation, and the magnitude of data need to be evaluated carefully before the use of these type of devices [51].

The study will evaluate the balance of the participants via postural sway and FBG tests. The FBG test, specifically designed for older people, will evaluate the static and dynamic balance and participant’s gait. Wearable devices make it possible to measure postural sway outside the laboratory setting, and an IMU is easy to transport and easy to use. Thus, the IMU is a novel tool for assessing postural sway in a clinical setting.

Randomization will be performed with block randomization to ensure an equal number of participants in each group. We expect that there might be more dropouts from the intervention including monitoring with an IMU. Therefore, we made a generous calculation of the dropout rate when calculating the sample size.

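### More dropout is anticipated in the wearable-device arm, but the only stated response is an equal margin of about 10% in every arm, and the named analyses do not by themselves deliver the promised intention-to-treat comparison

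*Protocol article*

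**What the plan says.** Section 2.9 (Statistics) compares the three groups by ANOVA if the data are normally distributed and by Kruskal-Wallis otherwise, followed by post-hoc tests. It mentions no covariate. It closes: "In all analysis, intention to treat will be used".

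Section 2.7 (Sample Size) bases the calculation on "a mean value of 1.8 mm/s for difference in postural sway in the anterior-posterior (AP) direction between two groups". It arrives at 43 per group for 80% power at a significance level of 0.017, then adds: "To compensate for dropouts, the sample size was set to 48 participants in each group". No dropout rate and no SD are given.

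Section 3 (Discussion) says: "We expect that there might be more dropouts from the intervention including monitoring with an IMU". The next sentence gives the response: "Therefore, we made a generous calculation of the dropout rate when calculating the sample size".

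Three other places bear on the point:
- Section 2.6 (Procedure) schedules all outcome measures at baseline and at the end of rehabilitation, with sway and balance again three months later. The treating physiotherapist notes who discontinues or deviates and why. The section does not say whether outcomes are still measured afterwards.
- Section 2.11 (Ethical Considerations) lets participants leave the study at any time.
- Section 2.10 (Feasibility Study) tests retention and the ability to collect outcomes before the full trial, and allows the protocol to be adjusted.

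**The concern.** The article anticipates that loss may depend on the arm and then treats this as a sample-size matter. Enlarging every arm equally restores numbers. It does nothing about who is left. If the people who leave arm B differ in balance from those who stay, and more of them leave B than the other arms, the groups measured at follow-up are no longer the groups that were randomised.

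The direction matters. The stated hypothesis is that HIFE with the wearable device does better than both standard rehabilitation and HIFE alone. If those who leave B are the frailer participants, the rest of B shows less sway and the error favours the hypothesised arm in both comparisons. If those who leave are the fast recoverers, the error runs the other way. The article gives no means of telling which applies.

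The allowance is also called generous and is linked by the word therefore to an expectation about one arm, yet it is the same in every arm and of ordinary size.

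**Working it through.** **1. The plan's own figures.**
- Significance level: 0.05/3 = 0.0167, rounded to 0.017.
- Implied dropout allowance: (48 − 43)/48 = 10.4%. A planned 10% gives the same number: 43/0.90 = 47.8, rounded up to 48. Total: 3 × 48 = 144, as in section 2.1.
- The 43 cannot be reproduced independently because no SD is stated. It can only be solved backwards. With the normal formula n = 2(z₁₋α/₂ + z₁₋β)²/d², two-sided α = 0.017 and 80% power, n = 43 requires d = 0.696, so SD = 1.8/0.696 = 2.59 mm/s. With the noncentral t distribution, d = 0.708 and SD = 1.8/0.708 = 2.54 mm/s. A one-sided test would imply 2.82 mm/s. I use 2.54 below. Two-sidedness is assumed, because the article does not state it.

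**2. Bias if only observed values are compared.** In an arm that loses a fraction p, the mean of those kept equals the mean of all randomised minus p × g, where g is the mean of those lost minus the mean of those kept. With the same g in both arms and no true difference, the comparison shifts by (p_B − p_comparator) × g. Taking g = 1 SD (assumed):

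| Loss in B v comparator | Shift | mm/s | Share of 1.8 |
|---|---|---|---|
| 20% v 10% | 0.10 SD | 0.10 × 2.54 = 0.25 | 14% |
| 25% v 10% | 0.15 SD | 0.15 × 2.54 = 0.38 | 21% |
| 30% v 10% | 0.20 SD | 0.20 × 2.54 = 0.51 | 28% |

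A milder model gives somewhat less. I simulated 48 per arm with no true effect, a correlation of 0.5 between propensity to drop out and outcome, and a completers-only t test at 0.017:

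| Loss in comparator v B | Shift in favour of B | mm/s (× 2.54) | Type I error |
|---|---|---|---|
| 10.4% v 10.4% | 0 | 0 | 1.7% |
| 10.4% v 25% | 0.11 SD | 0.28 | 3.2% |
| 10.4% v 30% | 0.15 SD | 0.38 | 4.2% |
| 5% v 30% | 0.19 SD | 0.48 | 6.0% |

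The first row shows that equal loss with the same mechanism in both arms produces no bias. Unequal loss is what does the harm.

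**3. Power for B against one comparator** (d = 0.708, noncentral t, α = 0.017, comparator keeps 43 of 48):

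| Loss in B | Left in B | Power |
|---|---|---|
| 10.4% | 43 | 80% |
| 15% | 41 | 79% |
| 20% | 38 | 77% |
| 25% | 36 | 76% |
| 30% | 34 | 74% |

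If the comparator lost nobody and B lost 25% (36 v 48), power would be 78%. The power cost is modest.

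**4. What adjustment for baseline can do.** Baseline sway is measured before randomisation in everyone (section 2.8). In simulations with 30% v 10.4% loss, the completers-only comparison was biased by about 0.12–0.14 SD. Adjusting for baseline removed the bias when loss depended on baseline, removed part of it when loss depended on the outcome itself, and reduced the standard error.

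**The case against.** The strongest reply is that much of this is inferred from silence. A reader might infer three things that the article does not say:
- **That each visit is analysed on whoever happens to be measured.** Section 2.9 fixes no visit and no missing-data rule, and ANOVA or Kruskal-Wallis can follow imputation. A missing-data method may be in the analysis plan or full protocol, which are not shown, so its absence from a journal article is no finding.
- **That dropouts will be replaced.** Section 2.7 only enlarges the sample, which is ordinary practice and compatible with intention to treat.
- **That stopping the device counts as dropping out.** The Discussion does not define dropout. Section 2.6 speaks of discontinuing the intervention, and section 2.11 separately of leaving the study.

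The reply continues that the Discussion says only that there might be more dropouts in one arm, that the equal margin would suffice if B lost no more than about 10%, and that the feasibility study will check retention before the full trial.

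All of that stands, and it limits the point. It does not remove it. The article names a risk specific to one arm and names its remedy, and that remedy addresses power only. The feasibility study may correct the margin, but a better margin still would not protect the comparison.

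A further fair objection concerns remedies. A mixed model with baseline as a covariate is not enough. The first post-baseline measurement comes at the end of rehabilitation, so someone lost before then has no follow-up value and is dropped from such a model. Any such model also assumes data missing at random, so it does not correct loss that depends on the unobserved outcome. The fix takes account of both.

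**Conclusion.** The point holds in a limited form. The article anticipates more loss in arm B, responds only with an equal allowance of about 10%, and names unadjusted tests that do not by themselves give an intention-to-treat comparison when loss is unequal. It does not show that the trial will run a completers-only analysis.

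The main risk is bias in the two comparisons with B: roughly 0.1–0.2 SD, or about 0.3–0.5 mm/s, if B loses 25–30% and the others about 10% (5% in the most unequal case simulated). The loss of power is secondary, from 80% to about 74–76% for B against a comparator under 25–30% loss in B and 10.4% in the comparator. These sizes rest on assumed loss rates, an assumed link between loss and sway, and an SD solved backwards from the sample size. If loss in B turns out close to that in the other arms and arises in the same way, both effects largely vanish. The change is worth making before the full trial, because outcomes not collected after discontinuation cannot be recovered at analysis.

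**What to change.** 1. **Follow-up.** State that participants who stop the device or the exercise programme stay in the study, and that sway and FBG are measured at the planned follow-ups unless consent is withdrawn. Because the rehabilitation period varies by participant, also state how the end-of-rehabilitation measurement is dated for someone who stops early.
2. **Analysis.** Replace unadjusted ANOVA on observed values with a baseline-adjusted longitudinal model for sway and FBG that keeps every randomised participant. Either include the baseline value in the response vector or use multiple imputation that draws on baseline.
3. **Sensitivity.** Because that model assumes missing at random, add a delta-adjusted analysis in which missing arm-B values are given progressively worse sway, and report how far they must worsen before the conclusion changes.
4. **Wording of the margin.** Replace the description of the allowance as generous with the actual figure, about 10% per arm, and say that it will be revisited with the retention found in the feasibility study. For scale, keeping 43 evaluable in B would need 54 randomised to B at 20% loss (43/0.80), 58 at 25% (43/0.75) and 62 at 30% (43/0.70).

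Cost: a few sentences, slightly more analysis work, and follow-up visits for participants who have stopped the intervention.
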